## Abstract

**Background:**

The objective of Heart Health NOW (HHN) is to determine if primary care practice support—a comprehensive evidence-based quality improvement strategy involving practice facilitation, academic detailing, technology support, and regional learning collaboratives—accelerates widespread dissemination and implementation of evidence-based guidelines for cardiovascular disease (CVD) prevention in small- to medium-sized primary care practices and, additionally, increases practices’ capacity to incorporate other evidence-based clinical guidelines in the future.

**Methods/design:**

HHN is a stepped wedge, stratified, cluster randomized trial to evaluate the effect of primary care practice support on evidence-based CVD prevention, organizational change process measures, and patient outcomes. Each practice will start the trial as a control, receive the intervention at a randomized time point, and then enter a maintenance period 12 months after the start of the intervention. The intervention will be randomized to practices in one of four strata defined by region of the state (east or west) and degree of practice readiness for change. Seventy-five practices in each region with a high degree of readiness will be randomized 1:1:1 in blocks of 3 sometime prior to month 8 to receive the intervention at month 9, 11, or 12. An additional 75 practices within each region that have a low degree of readiness or are recruited later will be randomized 1:1 in blocks of 2 prior to month 13 to receive the intervention at month 14 or 16. The sites will be ordered within each strata based on time of enrollment with the blocking based on this ordering. Evaluation will examine the effect of primary care practice support on (1) practice-level delivery of evidence-based CVD prevention, (2) patient-level health outcomes, (3) practice-level implementation of clinical and organizational changes that support delivery of evidence-based CVD prevention, and (4) practice-level capacity to implement future evidence-based clinical guidelines.

**Discussion:**

Results will indicate whether primary care practice support is an effective strategy for widespread dissemination and implementation of evidence-based clinical guidelines in primary care practices. Discernible reductions in cardiovascular risk in 300 practices covering over an estimated 900,000 adult patients would likely lead to prevention of thousands of cardiovascular events within 10 years.

**Trial registration:**

ClinicalTrials.gov NCT02585557

**Electronic supplementary material:**

The online version of this article (doi:10.1186/s13012-015-0348-4) contains supplementary material, which is available to authorized users.

## Background

Cardiovascular disease (CVD) is the leading cause of death in the USA [1]. CVD imposes a staggering burden whether measured in life-years lost, diminished quality of life, racial and ethnic health disparities, or direct and indirect healthcare costs. Yet, the Centers for Disease Control and Prevention (CDC) estimates that more than 200,000 deaths from heart disease and stroke could be prevented each year through a concerted, national effort to control CVD risk factors such as blood pressure, cholesterol, and tobacco use.

In September 2011, the US Department of Health and Human Services launched the “Million Hearts” initiative to prevent 1 million heart attacks and strokes by 2017 [2]. In the clinical realm, Million Hearts focuses on the management of the “ABCS”—aspirin use in high-risk individuals, blood pressure control, cholesterol management, and smoking cessation [2]. To support Million Hearts, the US Agency for Healthcare Research and Quality (AHRQ) launched an initiative in 2015 to assist primary care practices in implementing clinical and organizational changes to improve the management of ABCS.

### Objectives and aims

Heart Health NOW (HHN), an AHRQ-funded demonstration and evaluation, investigates whether a comprehensive evidence-based quality improvement strategy (which we call primary care practice support) accelerates the implementation of evidence-based guidelines for CVD prevention in primary care practices on a large scale. The specific aims are to evaluate the effect of primary care practice support in small- to medium-sized practices on (1) practice-level delivery of evidence-based CVD prevention, (2) patient-level health outcomes, (3) practice-level implementation of clinical and organizational changes that support delivery of evidence-based CVD prevention, and (4) practice-level capacity to implement future evidence-based clinical guidelines. HHN is a cooperative effort of the University of North Carolina at Chapel Hill (UNC-CH), the North Carolina Area Health Education Center (NC AHEC), and Community Care of North Carolina (CCNC), the primary care case management provider for NC Medicaid.

## Methods/Design

### Study setting

North Carolina is the tenth largest state in the USA with a population approaching 10 million and a racial and ethnic composition of 72 % white, 22 % black, and 9 % Hispanic [3]. The burden of cardiovascular disease in North Carolina remains large. The cardiovascular death rate was 263 per 100,000 as measured in 2008–2010, accounting for almost one-third of deaths in the state. These data rank North Carolina 32nd among the 50 states for cardiovascular outcomes [4].

### Research design

HHN is a stepped wedge, stratified, cluster randomized trial. Each practice will start the trial as a control, receive the primary care practice support intervention at a randomized time point, and then enter a maintenance period 12 months after the start of the intervention. The intervention will be randomized to practices in one of four strata defined by region of the state (east or west) and degree of practice readiness for change (described below). Specifically, 75 practices in each region with a high degree of readiness will be randomized 1:1:1 in blocks of 3 prior to month 8 to receive the intervention at month 9, 11, or 12. An additional 75 practices within each region that have a low degree of readiness or are recruited later will be randomized 1:1 in blocks of 2 prior to month 13 to receive the intervention at month 14 or 16. The sites will be ordered within each stratum based on time of enrollment with the blocking based on this ordering. The study’s statistician will generate the stratified permuted-block random allocation lists using a computer program. As practices are enrolled, the project management system will use the randomization schedule to randomize practices and assign their intervention start date. A practice is considered randomized once an intervention start date has been assigned. Neither study personnel nor participating practices will be blind to randomized start dates.

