### Practice recruitment

We will recruit 300 small- to medium-sized primary care practices. To be eligible, practices must have ten or fewer providers in a single location and have an electronic health record (EHR). Enrolling practices agree to the following: (1) form a quality improvement team; (2) meet with the practice facilitator up to 8 h a month; (3) send representatives to regional learning collaboratives three times yearly; (4) meet with experts to discuss CVD prevention, CVD risk assessment, and system change strategies; (5) permit the CCNC Informatics Center to process EHR data and provide the practice with cardiovascular care registries and dashboards for clinical decision support and population health management; (6) review data on ABCS measures at least monthly; and (7) use those data to plan, conduct, and assess improvement activities. Enrolling practices complete an information technology and quality improvement readiness assessment, which is used for earlier randomization of high-readiness practices and assignment of practices to more or less intensive practice facilitation.

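### Fixed blocks of 2 and 3, assigned openly in enrollment order, let anyone tracking a stratum deduce 41% of start dates in advance

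*Protocol article*

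**What the plan says.** All of the allocation procedure is in the Research design section of the protocol article.

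- **Strata.** Practices fall into "one of four strata defined by region of the state (east or west) and degree of practice readiness for change".
- **Three-step strata.** "75 practices in each region with a high degree of readiness will be randomized 1:1:1 in blocks of 3 prior to month 8", with start months 9, 11 and 12.
- **Two-step strata.** The less ready and late-enrolling practices, again 75 per region, "will be randomized 1:1 in blocks of 2 prior to month 13 to receive the intervention at month 14 or 16".
- **Order.** "The sites will be ordered within each stratum based on time of enrollment with the blocking based on this ordering".
- **Timing.** "As practices are enrolled, the project management system will use the randomization schedule to randomize practices and assign their intervention start date".
- **Openness.** "Neither study personnel nor participating practices will be blind to randomized start dates".

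The study statistician generates the permuted-block lists by computer. The section describes no variation in block size and no step that hides the next assignment from enrolling staff. The Trial status section says that recruitment was under way when the article, with its block sizes, was written.

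**The concern.** Each block is as small as it can be: it holds each start date once. With rolling assignment, open dates and a known block size, the end of a block can be deduced without seeing the list, so keeping the list with the statistician or in a management system does not protect it. A person who knows that the next slot in a stratum is an early or a late date could bring one practice forward or let another wait.

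The stake is the secular trend. Under Statistical analysis for Aim 1, each practice has one control measurement, at its own start month. After that, calendar time and time since start advance together within the practice. Model (1) also adjusts for region, readiness and their interaction. What remains to identify the linear part of the trend is the comparison of practices with different start months in the same stratum. That comparison is unbiased only if start month is unrelated to practice performance, which is what concealed allocation protects.

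**Working it through.** **Inputs.** Research design gives four strata of 75 practices, block sizes 3 and 2, start months 9/11/12 and 14/16, and rolling, unblinded assignment. Statistical analysis for Aim 1 gives model (1). Statistical power for Aim 1 gives the random-intercept variance 0.42 and β3 = 0.05.

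**1. Total.** 4 × 75 = 300, which matches Practice recruitment: "We will recruit 300 small- to medium-sized primary care practices".

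**2. Dates that can be deduced.** With known block size b and visible earlier assignments, the last practice in each complete block is determined, so the count per stratum is floor(75/b).
- Blocks of 3: 75/3 = 25 per region; 50 of 150 (33.3%).
- Blocks of 2: 75/2 = 37 complete blocks with one practice left over per region; 74 of 150 (49.3%).
- Overall: 50 + 74 = 124 of 300 (41.3%).

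The second practice in each block of 3 (50 practices) has two options left instead of three.

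**3. Guessing accuracy.**
- Blocks of 3: (1/3 + 1/2 + 1)/3 = 61.1%.
- Blocks of 2: (37 × 1.5 + 0.5)/75 = 74.7%.
- Overall: 67.9%, against (150/3 + 150/2)/300 = 41.7% by chance.

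**4. Sensitivity to the split.** If 45 to 90 practices per region were high-readiness, with the total still 300, the deducible share runs from 44.7% down to 40.0%.

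**5. How a gradient would enter the effect.** Write calendar time as t* = s + t, where s is the start month and t the time since start. Suppose that within strata the practice level on the logit scale rises by δ per start month, that the true secular trend is flat, and that the true intervention curve is f(t). Then

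δs + f(t) = δ(s + t) + [f(t) − δt].

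A model with a linear calendar trend fits this exactly with trend slope δ, and the 12-month log odds ratio becomes f(12) − 12δ. The documents give no value for δ, so these are assumptions:
- δ = 0.005: shift 0.06
- δ = 0.01: shift 0.12
- δ = 0.02: shift 0.24

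For scale, the power simulation uses β3 = 0.05. A δ of 0.01 is a difference of 0.03 logit between month-9 and month-12 practices, or about 0.62 × 0.38 × 0.03 = 0.7 percentage points at 62% control.

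**6. Comparison with chance.** The within-stratum sum of squares of start month is 50 × 4.67 + 75 × 2 = 383. Using the random-intercept variance alone, the chance gradient under perfect concealment has a standard error of √0.42/√383 = 0.648/19.6 = 0.033 logit per month. Over 12 months that is about 0.40.

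**7. Effect of varying the blocks.** A simulation with undisclosed random blocks of 3 or 6 and of 2 or 4, and staff who know the candidate sizes, left 8.6% and 10.9% of dates certain in advance: about 10% overall. One draw per stratum after enrollment closes leaves none.

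**The case against.** **Batch reading.** The deadlines before month 8 and month 13, together with ordering by enrollment time, could describe one draw at window close. Nothing would then be predictable at enrollment. The sentence on assigning dates as practices are enrolled points the other way, and the deadlines do not override it. If one draw was intended, the article should say so.

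**Weak motive.** Every practice receives the intervention, and dates within a stratum differ by at most 3 months (9 to 12) or 2 months (14 to 16). Nothing suggests that enrolling staff know a practice's baseline performance, and steering would need another practice from the same stratum to be held back. This stands, and it lowers the likelihood of bias. It does not remove the predictability, and the narrow window is what magnifies any imbalance that does occur.

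**Size of the illustration.** The assumed gradient of 0.01 is about a third of the chance gradient (0.033), so much of what step 5 shows is how weakly the linear trend is identified. Changing the blocks does not cure that. This stands too. The distinction is that chance imbalance under concealed allocation is part of the random variation that the analysis allows for, whereas steering would add a systematic shift. A shift this small would not be visible in a baseline table.

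**Readings that go too far.** A reader might infer that recruiters judge readiness and decide when a practice counts as enrolled. The article does not say this: under Practice recruitment, practices complete the readiness assessment, and nobody is named as controlling enrollment timing. A reader might also infer that the trend is identified from baseline differences alone. Model (1) shares its intervention and maintenance curves across practices, so contrasts between start months contribute at every visit.

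**Conclusion.** The point holds as a weakness in allocation concealment that the design permits. There is no evidence that selection took place. On the article's wording, 124 of 300 start dates (41%) can be deduced in advance and 50 more are narrowed from three options to two. This assumes rolling assignment, fixed blocks known to enrolling staff, and staff who track earlier assignments in their stratum; the article does not say that they do, or that they hold the list.

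The 0.12 shift is arithmetic on an assumed gradient and should not be read as an estimate of bias. What the documents do support is the mechanism: a within-stratum association between start month and practice performance is multiplied by 12 in the log odds ratio of primary interest.

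A minor note: 75 is odd, so blocks of 2 give 38:37 with one incomplete block per region. A reader might take this as a flaw in the design, but its effect on balance and power is negligible.

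Overall this is a modest issue, worth correcting because the correction is cheap.

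**What to change.** - **Preferred.** Randomize each stratum, or each stratum not yet allocated, in one draw when its enrollment window closes: before month 8 for the high-readiness strata and before month 13 for the others. Trial status puts month 9 at January 2016, so month 13 is May 2016, and the 150 low-readiness or later-recruited practices are the ones most likely to be still open to this change.
- **If dates must be issued on a rolling basis.** Use randomly varying block sizes (3 or 6, and 2 or 4), with the sequence of sizes not disclosed to enrolling staff.
- **Wording.** State whether assignment is rolling or in one draw, and note the 38:37 split in the two-step strata.

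The cost is a change to the allocation program. One draw gives practices shorter notice; for month-9 starters drawn just before month 8, roughly one month. Varying blocks loosen balance slightly and still leave about 10% of dates predictable.

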### Practice recruitment

We will recruit 300 small- to medium-sized primary care practices. To be eligible, practices must have ten or fewer providers in a single location and have an electronic health record (EHR). Enrolling practices agree to the following: (1) form a quality improvement team; (2) meet with the practice facilitator up to 8 h a month; (3) send representatives to regional learning collaboratives three times yearly; (4) meet with experts to discuss CVD prevention, CVD risk assessment, and system change strategies; (5) permit the CCNC Informatics Center to process EHR data and provide the practice with cardiovascular care registries and dashboards for clinical decision support and population health management; (6) review data on ABCS measures at least monthly; and (7) use those data to plan, conduct, and assess improvement activities. Enrolling practices complete an information technology and quality improvement readiness assessment, which is used for earlier randomization of high-readiness practices and assignment of practices to more or less intensive practice facilitation.

### Primary care practice support intervention

Practice facilitators will work for 12 months with practices’ quality improvement teams to implement four “key drivers” for supporting delivery of evidence-based CVD prevention: enhanced clinical information systems with dashboards on critical measures and drill downs to patient-level care; adoption and use of practice-wide evidence-based protocols; effective use, documentation, and tracking of patient self-management support goals; and optimization of the practice care team. Practices will receive up to 8 h a month of practice facilitation depending on their level of readiness at enrollment. In addition, physician faculty will engage in academic detailing through webinars and practice visits. Detailing will focus on CVD prevention and treatment, CVD risk assessment, and new recommendations for cholesterol and hypertension management. Finally, providers and staff will participate in regional learning collaborative meetings where they can share experiences implementing evidence into practice.

### Evaluation framework

Our evaluation draws on an organizational model of innovation implementation [5–9]. The innovation here is evidence-based CVD prevention (including clinical decision support and population health management tools, global risk-based treatment of lipids, new treatment options, and evidence-based smoking cessation). Briefly, effective implementation is a function of the implementation support the practice receives and the policies and practices it employs to support innovation use (see Fig. 1). Practice capacity for QI, readiness for change, and implementation climate moderate the relationship between support, policies and procedures, and effectiveness. Inner and outer contextual factors influencing organizational priorities, capabilities, and opportunities also moderate the relationship. Realization of patient- and practice-level benefits depends on effective implementation of evidence-based CVD prevention.

**Fig. 1 Fig1:**
[figure not shown]
Conceptual framework guiding the evaluation of Heart Health Now

### Data collection

Table 1 outlines data collection, measures, sources, and timing for each construct.

**Table 1 Tab1:** Theoretical constructs, measures, data sources, and data collection timing

Construct	Measures	Source	Timing
Implementation support	Frequency, duration, and mode of PF contacts	PF contact logs	I
	Frequency, duration, and mode of academic detailing contact	Contact, webinar logs	I
	Attendance at regional collaborative meetings	Attendance logs	I
Practice capacity for QI	Change Process Capacity Questionnaire	KI survey	B, E, F
	Adaptive Reserve Questionnaire	Provider/staff survey	B, E, F
Organizational readiness	Organizational Readiness for Change Questionnaire (ORIC)	Provider/staff survey	B
Implementation Policies and Practices (IPPs)	Key Driver Implementation Scales	PF Ratings	I
	Implementation barriers, facilitators, and IPPs	KI interview	B, E
Implementation climate	Implementation climate questionnaire	Provider/staff survey	E, F
Implementation effectiveness	ABCS measures/clinical measures	HIE	B, I, E, F
	Acceptability of implementation support	KI interview	E
Innovation effectiveness	Patient outcomes (communication, shared decision-making)	Patient survey	B, E
	Patient outcomes (healthcare utilization and mortality)	Claims data	B, E, F
	Practice outcomes (e.g., financial benefits)	KI Interview	E, F
Inner context	Practice characteristics, patient population, EMR capabilities	KI survey, PF contact logs	B, E,F
Outer context	External policies and incentives, market conditions	KI survey, KI interview, PF contact logs	B, E, F

Because readiness is conceived as an organization-level construct, we will test whether sufficient inter-rater reliability and inter-rater agreement exist to aggregate individual responses to the practice level [22–26]. If tests do not justify aggregation, we will use a measure of intra-practice variability in readiness rather than a practice-level mean in our analysis [15, 16].

Source: *PF* practice facilitator, *KI* key informant; timing: *B* baseline, *I* intervention, *E* end of intervention, *F* 6 and 12 months post-intervention

#### Practice facilitator contact logs

Practice facilitators (PFs) will record monthly the frequency, duration, and mode of practice contact. We will use these data to measure the intensity of implementation support provided to practices.

#### Academic detailing logs

Physician faculty will record visits, calls, and other contacts with practices. Webinar software will track logins and pages viewed by practice staff.

#### Regional collaborative attendance records

Project staff will keep records of the number and types of staff from each practice that attend regional collaborative meetings.

#### Key informant surveys

We will survey key informants (KIs) to assess practice capacity for QI, inner context, and outer context. The surveys will be administered at baseline, end-of-intervention, 6 months post-intervention, and 12 months post-intervention for practices enrolled earlier in the study. The KI will be the practice’s provider champion (*N* = 300).

#### Provider/staff survey

We will survey providers and staff to assess practice capacity for QI at baseline, end-of-intervention, 6 months post-intervention, and 12 months post-intervention for practices enrolled earlier; organizational readiness to implement change at baseline; and implementation climate at end-of-intervention and 6 months post-intervention. The sample will consist of 3–5 providers and staff members depending on practice size (*N* = 900–1500).

#### PF ratings

PFs will assess on a monthly basis practices’ progress in implementing clinical practice and organizational changes to support improvement in CVD prevention (implementation policies and practices). Ratings will focus on the extent to which practices have implemented four key drivers of improved CVD prevention and also level of leadership and team engagement.

